#### Objective 3: Assess Effects of Day Programs

To create a propensity score, we will run a logistic regression for each province with day program attendance or nonattendance as the dependent variable and adding matching covariates. We will use one-to-one matching (1 matched nonattendee for every attendee) [78]. We will use matching without replacement [85] and apply an optimal caliper matching algorithm [86]. As per best practice recommendations [87], we will use a caliper width of 0.2 of the SD of the propensity score’s logit. If this matching approach does not allow us to achieve a sufficient sample size, we will use propensity score quintiles for matching.

We will compare sample characteristics and study outcomes between attendees and nonattendees in every year and province, using bivariate statistical tests (eg, chi-square test or Fisher exact test for categorical variables, *t* tests, or ANOVAs for continuous variables, and their nonparametric equivalents if variables violate statistical assumptions). To assess the effect of day program exposure on time to care home admission, we will specify a multilevel time-to-event model with a health region–level random effect [88]. Health systems in each of the 3 provinces are divided into 5 health regions [89-91], and regional policies may cause clustering effects that our models must account for. Each model will include day program use or nonuse class as independent variable and will be adjusted for time-varying variables. These will include matching variables, if appropriate (ie, in case of group differences in matching variables over time or due to missing data) [80-82] and, if needed, additional covariates (eg, demographics, social determinants, medical or functional conditions, and non–day program community care). Covariates that differ between attendees and nonattendees with a *P* value of ≤.15 in the bivariate analyses will be considered for inclusion. We will add covariates stepwise, one-by-one, and remove those that cause collinearity issues or decrease model fit. As in objective 2, we will pool provincial effects statistically, using random-effects mixed regression models.

Using GEEs and a similar approach as for the time-to-event models (including separate models in each province and statistical pooling of their effects), we will assess whether the other study outcomes differ by day program use or nonuse pattern. Models will include each study outcome of interest as a dependent variable, day program use or nonuse class and time of assessment as independent variables, and similar covariates (using the same stepwise approach) as the time-to-event models. Models will also include a random term to account for repeated measures within individuals. The choice of a link function will be informed by the nature of the variable and theoretical and empirical considerations. For example, the number of hospital, emergency department, or physician visits has been shown to follow a zero-inflated negative binomial distribution, sometimes requiring an offset for the natural logarithm of person-time [92]. For continuous outcomes (eg, days spent in hospitals), we will use an identity link function, and for dichotomous outcomes (eg, presence or absence of depressive symptoms), we will use a logit link function. All models will apply multiple imputation in case of missing data, which we expect to be small based on our previous work with the administrative health care data sources used in this study.

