Explore patterns of day program use (eg, variations in time to first attendance, monthly hours of attendance, ongoing versus interrupted attendance, and total time of day program exposure), using latent class analyses (LCA), and compare the frequency of each latent use class between provinces and over time.Compare older adults’ demographic, social, and health characteristics (eg, age, sex, physical or cognitive disability, area-based deprivation indices, and caregiver availability or distress) by day program use or nonuse class, province, and time.Assess whether, compared with a propensity score–matched control group of nonattendees, day program attendees enter care homes at later points in time; use emergency, acute, or primary care less frequently; experience less cognitive and physical decline; have better mental health; and have less distressed caregivers. We will assess potential modification of these effects by day program use or nonuse class, age, sex, and social determinants of health (eg, area-based deprivation indices).

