#### Propensity Score–Matching Variables

To compare outcomes between day program attendees and nonattendees, we will use propensity score matching [78] (for details, see Statistical Analyses section). Propensity scores aim to ensure a similar distribution of baseline variables among treatment (day program attendees) and control (nonattendees)—akin to what random assignment aims to accomplish in randomized trials [78]. Since we lack evidence on differences between day program attendees and nonattendees, our objective 2 analyses will be key to informing the selection of the exact covariates that will form the propensity score. We will derive covariates for day program attendees from the RAI-HC day program eligibility assessment (index date). For each day program attendee, we will identify potential matches as nonattendees whose first RAI-HC assessment was completed within ±3 months of the attendee’s index date (ie, admission to long-term home care at about the same time). This RAI-HC assessment will provide the relevant covariates to enable propensity score matching with day program attendees as of their index date.

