Our first set of matching covariates will be RAI-HC variables used by health systems to determine day program eligibility [60,65,66]: physical functioning (ADLh Scale), cognition (CPS), behavioral symptoms (Aggressive Behavior Scale [79]), bladder or bowel continence (items I1, I3), availability of a caregiver (item G1e), and caregiver distress (items G2a-c). This will ensure that control participants are potentially eligible to a day program. Possible reasons for nonattendance include the lack of day program spaces, preference not to attend, inability to afford the required copayments, or not receiving a day program referral. Our experts assure us that the pool of potential matches far exceeds that of attendees, supporting the feasibility of this study and underscoring the lack of day program spaces. This approach excludes individuals whose care needs are either too low or too severe for day program eligibility, but it minimizes confounding by the matched variables and ensures comparable groups at baseline [80-82]. Finally, we will include a second set of matching covariates: health and social characteristics identified in objective 2 by which attendees and potentially eligible nonattendees differ and that overlap sufficiently between attendees and nonattendees (eg, age, sex, type or duration of publicly funded community care received before the matching index date, and deprivation indices).

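### Effect modification by sex, age and deprivation can be distorted because matching uses one score per province and neither balance nor adjustment is secured within modifier levels

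*Protocol article*

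**What the plan says.** The third research objective, at the end of the Introduction, commits the study to subgroup questions: "We will assess potential modification of these effects by day program use or nonuse class, age, sex, and social determinants of health". The same objective defines the comparison as one against propensity score-matched nonattendees.

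The section on Objective 3 under Statistical Analyses fixes the matching:

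- The score: "To create a propensity score, we will run a logistic regression for each province with day program attendance or nonattendance as the dependent variable".
- The ratio: "We will use one-to-one matching (1 matched nonattendee for every attendee", without replacement.
- The caliper: "we will use a caliper width of 0.2 of the SD" of the logit of the score.
- The fallback if too few pairs are found: "we will use propensity score quintiles for matching".

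The section Propensity Score–Matching Variables adds a calendar condition on potential controls: "nonattendees whose first RAI-HC assessment was completed within ±3 months" of the attendee's index date. The first covariate set is the eligibility measures (function, cognition, behaviour, continence, caregiver availability and distress). Age, sex and deprivation appear as examples in a second set. Its members must differ between the groups in objective 2 and be ones "that overlap sufficiently between attendees and nonattendees (eg, age, sex", among others.

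The outcome models are adjusted, but conditionally. On the matching variables the plan says: "These will include matching variables, if appropriate (ie, in case of group differences in matching variables over time or due to missing data"). Other covariates are considered when attendees and nonattendees differ at P ≤ .15 in bivariate comparisons made by year and province.

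**The concern.** A propensity score is sure to balance covariates within levels of a baseline modifier only if the score model is right about how attendance depends on the covariates at each level. Suppose caregiver distress drives attendance strongly in one sex and weakly in the other, and the score carries one common slope. Matched attendees will then be more distressed than their controls in one sex and less distressed in the other. The two errors cancel in the pooled sample.

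Both planned safeguards look at the pooled sample (by year and province), so neither is aimed at this pattern. Opposite residual confounding in two subgroups goes straight into the interaction term. The Introduction lists poorly understood differential effects as one of four knowledge gaps, so the equity conclusions could be wrong even where the overall effect is right.

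**Working it through.** **The plan's own figures.** The document gives no figure on subgroup balance. Its one calculated sample size (1327 for a hazard ratio of 0.6) concerns the overall effect and plays no part here.

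**Inputs from the document.** One score per province, 1:1 matching without replacement, caliper 0.2 SD of the logit, P ≤ .15 screen on pooled group differences.

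**Assumed inputs (not in the document).** 20,000 people, 60% women, about 2,200 matched pairs, and two standard normal covariates x and w. The attendance logit is

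-2.3 + 0.2·sex + 0.4·x + 0.3·w + g·(sex - 0.6)·x.

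The hazard is 0.08·exp(ln 0.8·attend + 0.5·x + 0.2·w - 0.1·sex), so the true hazard ratio is 0.8 in both sexes and the true ratio of hazard ratios is 1.00. The score has main effects of x, w and sex. Greedy nearest-neighbour matching stands in for the optimal algorithm. Each scenario had 20 runs.

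**Slopes of x on attendance implied by g.**
- g = 0.3: men 0.4 - 0.3×0.6 = 0.22; women 0.4 + 0.3×0.4 = 0.52.
- g = 0.5: men 0.4 - 0.5×0.6 = 0.10; women 0.4 + 0.5×0.4 = 0.60.

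**Results, outcome model without covariates** (SMD is the standardized mean difference in x, attendee minus control):

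| Scenario | SMD overall | SMD men | SMD women | HR men | HR women | Ratio (women/men) |
|---|---|---|---|---|---|---|
| g = 0 | 0.00 | -0.01 | 0.01 | 0.79 | 0.82 | 1.04 |
| g = 0.3 | 0.00 | -0.19 | 0.10 | 0.74 | 0.84 | 1.13 |
| g = 0.5 | 0.00 | -0.29 | 0.14 | 0.72 | 0.87 | 1.21 |
| g = 0.5, sex left out of the score | 0.00 | -0.31 | 0.17 | 0.69 | 0.89 | 1.28 |

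At g = 0.5 with sex in the score, the interaction test rejected at the 5% level in 40% of runs (8 of 20, so rough).

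**Check by hand.** The false ratio should be near exp{0.5 × (SMD women - SMD men)}. For g = 0.3: exp{0.5 × (0.097 + 0.186)} = exp(0.1415) = 1.15. For g = 0.5: exp{0.5 × (0.141 + 0.287)} = exp(0.214) = 1.24. The simulated 1.13 and 1.21 are slightly smaller and agree in direction and order.

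**Would the planned trigger fire?** In separate runs with slope differences of 0.3 and 0.6, the pooled baseline comparison of the covariate reached P ≤ .15 in 0 of 40 runs in each scenario, with SMDs of -0.18/+0.11 and -0.35/+0.20 in men/women.

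**What removes the false interaction (g = 0.5).**
- Sex-by-x term in the score: SMDs about 0.01 in both sexes, ratio 0.98.
- Separate matching within sex: SMDs about 0.00, ratio 1.03.
- Matching left as it was, outcome model adjusted for x and w: ratio 1.00 (0.99 at g = 0.3).

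**The case against.** The case on the other side has four parts.

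**Discordant pairs.** A reader might infer that pairs are biased because their members can differ in sex. That does not follow. With g = 0, 44% of pairs were of discordant sex and balance within sex was still good. The mechanism is an omitted interaction, not discordance.

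**The omission is not documented.** The article says only that matching covariates are added to the logistic model, and it leaves their choice to objective 2. It does not say main effects only, and nothing in it shows that determinants of attendance differ by sex, age or deprivation. It is also a condensed text, so silence on interaction terms or subgroup balance tables is not in itself an error. This stands, and it makes the bias conditional.

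**Adjustment is planned.** A reader might infer that modification will be read from raw pairs. The article does not describe the interaction analysis. Its outcome models are covariate-adjusted, and in the simulation full adjustment removed the problem. The trigger also covers differences that arise over time and is applied by year and province, so it could fire. This stands in part: it would fire only incidentally, because no trigger is evaluated within a modifier level.

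**Matching is not on one undifferentiated score.** It is done within province and within a ±3-month window, and the modifiers may be in the score. That is correct, but neither condition secures balance within sex, age or deprivation groups.

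**Conclusion.** The point holds in conditional form. The plan states a subgroup objective, then fixes a matching design and adjustment triggers that act on attendees against nonattendees as a whole. If determinants of attendance differ by modifier level and the score omits those terms, false effect modification can result, and the planned checks may not show it.

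Under the assumed parameters, the false ratio of hazard ratios is about 1.13 for a slope difference of 0.3 and 1.21 for 0.5. It is negligible when there is no such difference or when the outcome model adjusts for the affected covariates. These sizes rest on one interacting covariate with an assumed log hazard ratio of 0.5 per SD and on few runs. They show the order of magnitude, not a forecast.

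The documents do not support saying that the subgroup results will be wrong, or that the overall effect is affected by this mechanism. It is an improvement worth making before the shared programs are run, not a fatal flaw.

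**What to change.** In the Objective 3 section, for the effect-modification analyses:

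1. Include modifier-by-covariate interaction terms in the propensity model, at least for the eligibility covariates, or match separately within sex.
2. Check covariate balance within each level of sex, age band and deprivation group before outcomes are examined, and refit the score if it fails.
3. Adjust every interaction model for the eligibility covariates listed under Propensity Score–Matching Variables, regardless of the P ≤ .15 screen.

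Exact matching on sex is optional and cheap, since the article states that potential matches far exceed attendees. Exact matching on every age and deprivation band should not be required. With four deprivation indices in three groups each, three age bands and two sexes there would be 3×3×3×3×3×2 = 486 cells per province, before the calendar window and caliper apply.

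The cost is a little more analysis work, written once because the provinces use shared programs, and possibly a few unmatched attendees. In simulation, over 99% of attendees were still matched with interaction terms or with matching within sex.

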### Data Sources

For each individual in our cohort, designated provincial health system analysts will link all records available within the study time frame from the following databases: (1) regional continuing care registries, documenting when an individual starts or stops receiving any community-based continuing care, including day programs, how these services change over time, and when an individual is admitted to a care home. (2) Population registries for each participant’s demographic data. (3) RAI-HC assessments [64], completed annually for people receiving long-term home care (60+ days), and to determine day program eligibility. The RAI-HC will provide data on older adults’ medical conditions, functional dependence, pain, cognitive impairment, mood, and behavioral problems. It also includes information on a person’s marital or partnership status, caregiver availability, whether that caregiver lives with the older adult, and caregiver distress. Additional caregiver characteristics are not included in the available provincial databases, posing a limitation to our quantitative analyses. However, a related prospective cohort study that we are conducting in Ontario will allow us to link comprehensive caregiver and older adult data, and we are currently conducting additional qualitative research that will illuminate how caregiver characteristics may affect day program use and outcomes. (4) Discharge abstract database (DAD) for information on all inpatient hospital stays, including diagnoses and length of stay. (5) National Ambulatory Care Report System (NACRS) for all emergency department visits and diagnoses. In British Columbia, we will use the physician payment file in addition, since NACRS is not collected in all emergency departments [70]. (6) Pharmaceutical information on outpatient prescription medications filled through a community pharmacy and covered by provincial drug formulary. (7) Care provider claims data for health service claims submitted for payment by health care providers (eg, general practitioners, nurse practitioners, geriatricians, geriatric psychiatrists, neurologists, therapists) to obtain information on general and specialist health services used by participants.

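### Health region is named neither in the province-wide matching nor in the GEE outcome models, so regional differences could be read as a program effect

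*Protocol article*

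**What the plan says.** **Matching.** Under Objective 3 of the Statistical Analyses, the protocol article states: "we will run a logistic regression for each province with day program attendance or nonattendance as the dependent variable and adding matching covariates". Matching is one-to-one, without replacement, with a caliper. Under Propensity Score–Matching Variables, potential controls are "nonattendees whose first RAI-HC assessment was completed within ±3 months of the attendee’s index date"; no geographic limit is given.

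**Covariates.** "Our first set of matching covariates will be RAI-HC variables used by health systems to determine day program eligibility": function, cognition, behaviour, continence, caregiver availability and caregiver distress. The second set is to come from Objective 2. Its examples are age, sex, earlier community care and deprivation indices. The section on demographic, social and health characteristics, which feeds that set, does not list health region either.

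**Region.** The Objective 3 section notes five health regions per province and says "regional policies may cause clustering effects that our models must account for". It gives the time-to-admission model a health region random effect. For the other outcomes, analysed by GEE, the approach is described as similar, and the term specified is: "Models will also include a random term to account for repeated measures within individuals".

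**Supply and data.** "Possible reasons for nonattendance include the lack of day program spaces", among other reasons. Under Data Sources, British Columbia adds the physician payment file "since NACRS is not collected in all emergency departments". The Study Outcomes section derives emergency rates from the DAD and NACRS and does not mention that file.

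**The concern.** If attendance differs between regions of a province, and care use or its recording also differs between them, region is a common cause of exposure and measured outcome. Matching that ignores region can then draw attendees mainly from some regions and controls mainly from others. Balance on individual eligibility variables does not correct this. Deprivation indices describe small areas, not regional policy or program supply.

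For time to care home admission, the random effect conditions on region. For every other outcome no region term is named. The within-person term does not fill the gap: it allows for correlation among repeated measurements of one person and leaves regional differences in level untouched. A correction for clustering by region would not suffice either, because it repairs standard errors and not confounding. The plan expects more than 20,000 attendees a year, so even a modest bias would look statistically convincing.

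**Working it through.** The plan states no figure on this point, so there is none to reproduce. The check has three steps.

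**1. Where region appears**

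| Step | Region named? |
|---|---|
| Pool of potential controls | No; time window only |
| First matching set | No |
| Second matching set (open list of examples) | No |
| Objective 2 characteristics | No |
| Time-to-admission model | Yes, random effect |
| GEE outcome models | No; within-person term only |

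**2. What ignoring region could do (all inputs assumed)**

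Take five regions of equal size, a true ratio of 1, and controls drawn from nonattendees without regard to region. Let a be the proportion attending in a region and b its outcome rate. Then

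null ratio = [Σab / Σa] ÷ [Σ(1−a)b / Σ(1−a)].

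- *Equal attendance* (10% everywhere): 1.00 whatever the regional rates.
- *Mild*: attendance 5, 7.5, 10, 12.5, 15%; rates 10, 11, 12, 13, 14%. (0.0625/0.5) ÷ (0.5375/4.5) = 0.1250/0.1194 = 1.05. With the rates reversed: (0.0575/0.5) ÷ (0.5425/4.5) = 0.1150/0.1206 = 0.95.
- *Steep*: attendance 2, 5, 10, 15, 20%; rates 8, 10, 12, 14, 16%. (0.0716/0.52) ÷ (0.5284/4.48) = 0.1377/0.1179 = 1.17. With the rates reversed: (0.0532/0.52) ÷ (0.5468/4.48) = 0.1023/0.1221 = 0.84.

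The same formula applies to emergency visits if b is the share of visits recorded in a region. Regions are ordered as above, from lowest to highest attendance:

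| Assumed capture | Mild attendance | Steep attendance |
|---|---|---|
| 100, 100, 100, 90, 80% | 0.97 | 0.95 |
| 100, 100, 90, 70, 50% | 0.91 | 0.84 |
| 50, 70, 90, 100, 100% | 1.09 | 1.16 |

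Capture here means what remains after the payment file is added. The documents do not give its completeness.

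**3. What the random effect does for time to admission**

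The steep scenario with reversed rates was simulated 100 times: 2,000 people per group, constant hazards by region, three years of follow-up, true hazard ratio 1.

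- Without region: 0.84.
- With a region random intercept: 0.99.
- With region fixed effects: 1.00.

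The random-intercept variance was set from the assumed rates, not estimated. With regions this large there is little shrinkage, so a region term of either kind removes nearly all of the bias.

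**The case against.** Four points on the other side carry weight.

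- **The covariate list is open.** The second set is given by example, Objective 2 is to settle the exact covariates, and the Discussion plans a paper comparing use and nonuse by health region. Nothing excludes region. This stands, but nothing commits to it either, and region is absent from the characteristics that Objective 2 will examine.
- **The GEE wording may already cover it.** The article speaks of its models in the plural and calls the GEE approach similar to the time-to-event approach. That is a possible reading. However, the details it gives for that similarity concern province, and a random intercept does not carry over directly to a marginal model.
- **The bivariate comparisons are descriptive** and screen covariates; they are not the effect estimates. This stands, and the point does not rest on them.
- **Strict within-region matching has a price.** It reduces the use of controls who did not attend because their region lacked spaces. It leaves relatively more who declined, could not pay or were not referred. The statement that potential matches far exceed attendees is not made by region. This stands, and is why exact matching should not be mandatory.

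A reader might also infer that access rules, program spaces and emergency capture are all documented to vary within provinces. They are not. Access criteria are attributed to each provincial health system, and regional policies are only said to be a possible cause of clustering. Spaces are given as province totals, so local variation in supply is a reasonable inference and no more. Incomplete NACRS collection is stated for British Columbia alone, with a supplement, and no text links it to program supply.

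**Conclusion.** The point holds as a gap in handling region, chiefly for the GEE outcomes. Followed as written, pairs can cross regions, and no region term is named for any outcome except care home admission. This sits badly with the article's own statement that its models must account for regional policies.

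The documents do not support the stronger conclusion that the care home result is seriously biased by region. The planned random effect should deal with most of that, and emergency data capture has no bearing on it, because admissions come from the continuing care registries.

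The size of any bias cannot be computed: the documents give no attendance, outcome or capture rates by region. The illustrative ratios of 0.95 to 1.05 and 0.84 to 1.17 rest wholly on assumed inputs. They also assume that the other matching covariates carry no information about region; if prior care or deprivation does, the bias would differ. If attendance does not vary by region, this bias disappears.

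The change is worth making before the shared analysis programs are fixed. The gap does not invalidate the design.

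**What to change.** 1. Include health region of residence at the index date as a covariate in each province's propensity model, or match within region where the local pool allows. Report balance by region after matching.
2. Add region as a fixed covariate (five levels per province) to all GEE outcome models. The random effect in the time-to-admission model can stay.
3. Reconcile Data Sources with Study Outcomes, so that British Columbia emergency visits are counted from NACRS plus the physician payment file under one rule for attendees and controls.

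The cost is mainly programming, since region is already required for the planned random effect. A few attendees may go unmatched, and conditioning on region gives up some between-region variation in supply.
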